#### Sample size and power

Based on similar previous studies [35, 47], a sample size of 400 women is required to have 320 women completing the study with 215 receivers and 105 decliners (after adjusting for loss to follow up of approximately 20%). For a two sided test and based on a 5% significance level, this sample size will have 80% power to detect a clinically meaningful difference in the primary psychological outcome of breast cancer anxiety as measured by the IES (SD 14.2, range 0–75 scores) [48] at the 2-week follow-up, between affected and unaffected women who receive a high PRS result (hypothesis 2c). A difference of seven scores (half a standard deviation) on the IES is considered a clinically meaningful difference to detect [49].

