### Participants

#### Inclusion criteria

Approximately 400 women will be recruited to this study from the existing ViP cohort. Only women aged 18 years will be recruited. Both index cases and their affected and unaffected family members will be invited to participate in this study. Women will be eligible if they have either a low (*N* = 200) or a high PRS (*N* = 200). Each group will be stratified by disease status, such that about 100 affected and 100 unaffected women are included in each study group (Fig. 3).

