### Methodological strengths and limitations

A substantive strength of this study is the large and diverse cohort available through the parent ViP study. The parent study aims to recruit every family in Victoria and Tasmania that attended a FCC to undergo genetic testing for hereditary breast cancer. The multicenter approach and diverse cohort will increase the external validity and generalization of the study findings. The sample size in the current study will provide sufficient power to detect clinically meaningful effects for the key outcome variable of breast cancer anxiety.

The study is a prospective study, which employs, wherever possible, validated measures that have been utilized previously with women at high risk for breast cancer. In applying this study design we hope to build a comprehensive picture of the psychological and behavioral outcomes associated with receiving polygenic breast cancer risk information.

Two potential limitations of the study must also be acknowledged. Firstly, it was beyond the capacity of the research to translate the patient questionnaires into other languages. Hence, women from non-English speaking backgrounds cannot be included. Secondly, this study will not involve development and assessment of pre-testing genetic counselling as the PRS results are available as part of the parent ViP study. The focus of this translational research is to explore the uptake of PRS results and psychological and behavioral outcomes associated with receiving or not receiving one’s PRS result. Future research will be able to explore pre-testing genetic counselling and the informed consent process including the provision of information of the benefits and limitations of SNP testing.

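### The 80% power for hypothesis 2c is set beside a receiver count after loss (215) that gives about 72%; 80% holds only if almost no receiver is lost before week 2

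*Protocol article*

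**What the plan says.** All of the following is in the protocol article.

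- **Sample size and power, the counts.** 400 women are needed to obtain "320 women completing the study with 215 receivers and 105 decliners (after adjusting for loss to follow up of approximately 20" per cent). These are the only counts of receivers and decliners given.
- **Sample size and power, the claim.** The next sentence begins "For a two sided test and based on a 5% significance level" and continues "this sample size will have 80% power to detect a clinically meaningful difference in the primary psychological outcome of breast cancer anxiety". It names the comparison as affected versus unaffected women with a high PRS at the 2-week follow-up (hypothesis 2c). The inputs are "SD 14.2, range 0–75 scores" and a 7-point target: "A difference of seven scores (half a standard deviation) on the IES is considered a clinically meaningful difference to detect".
- **Inclusion criteria.** 200 low-PRS and 200 high-PRS women are planned, stratified by disease status so that "about 100 affected and 100 unaffected women are included in each study group".
- **Study design.** Receivers complete questionnaires at baseline, at 2 weeks and at 12 months after the result. Completing the study therefore means reaching 12 months.
- **Methodological strengths and limitations.** The sample size "will provide sufficient power to detect clinically meaningful effects for the key outcome variable of breast cancer anxiety".

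The article gives no number per group for hypothesis 2c and no loss figure for week 2. It does not say whether the 80% rests on receivers before or after loss.

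**The concern.** Sample sizes are inflated for loss so that the stated power holds in the women who remain. A reader will therefore take the receiver count labelled as after loss, 215, as the basis of the 80%. Only about a quarter of those receivers fall in each arm of the 2c comparison, and that is too few for 80% power at 7 points.

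This is the article's only power statement, and it concerns the primary psychological outcome. If all the loss fell before week 2, the chance of missing the article's own clinically meaningful difference would be about 28% instead of 20%. A null result on 2c would then be weaker evidence than the text suggests that affected women are no more distressed than unaffected women by a high PRS.

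**Working it through.** **Inputs**

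- From Sample size and power: difference 7, SD 14.2, two-sided 5%, stated power 80%, 400 women at the start, 320 completers, 215 receivers after about 20% loss.
- From Inclusion criteria: four PRS-by-disease cells of about equal size.
- Assumption, not in the document: uptake and loss are equal across the four cells, so each 2c group holds one quarter of the receivers.

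**Formulas.** The standardised difference is 7/14.2 = 0.493. The normal approximation is power = Φ(7 / (14.2 × √(2/n)) − 1.96), with n per group. The two-sample t-test was run as a check and is slightly lower.

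**Step 1: number needed for 80%.** n = 2 × (1.96 + 0.84)² × 14.2² / 7² ≈ 64.6, so 65 per group. The t-test gives 65.6, so 66 per group. Across four cells that is 4 × 65 = 260 to 4 × 66 = 264 receivers with 2-week data.

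**Step 2: reproducing the stated 80%.** Receivers before loss are 400 × 215/320 = 268.75, about 269, which is 67.2 per group. The standard error is 14.2 × √(2/67.2) = 2.45, and 7/2.45 − 1.96 = 0.90. Power is 81.5% (normal) or 81.0% (t-test). The stated figure is reproduced on this basis.

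**Step 3: the count printed beside the claim.** 215/4 = 53.75 per group. The standard error is 14.2 × √(2/53.75) = 2.74, and 7/2.74 − 1.96 = 0.60. Power is 72.4% (normal) or 71.6% (t-test). Taking exactly half an SD (7.1 points) gives 73.6% or 72.9%. The difference detectable with 80% power is 14.2 × (1.96 + 0.84) × √(2/53.75) = 7.7 points.

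**Step 4: power by loss before the 2-week questionnaire**, starting from 268.75 receivers (t-test):

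| Loss by week 2 | Per group | Power |
|---|---|---|
| 0% | 67.2 | 81.0% |
| 2% | 65.8 | 80.2% |
| 3% | 65.2 | 79.8% |
| 5% | 63.8 | 78.9% |
| 10% | 60.5 | 76.7% |
| 15% | 57.1 | 74.3% |
| 20% | 53.8 | 71.6% |

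A full 80% survives up to about 2% loss by the t-test (1 − 4 × 65.6/268.75 = 2.4%) and about 4% by the normal approximation (1 − 4 × 64.6/268.75 = 3.9%).

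**Step 5: other ways to reach 80%.**

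- A one-sided test with 54 per group gives 82%, but the text specifies two-sided.
- Taking all completers, 320/4 = 80 per group, gives about 87%, but 2c concerns receivers only.
- An uneven 40:60 split of affected and unaffected women lowers the after-loss figure to about 71% (normal approximation).

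**The case against.** The strongest reply concerns timing. The 20% loss is attached to completing the study, which for receivers means the 12-month questionnaire, while 2c is measured at 2 weeks. On that view 215 is a 12-month count. The 2-week number would lie nearer 269, and the stated 80% follows from the article's own figures. This largely stands. A reader might infer that the study has 72% power and that the 80% is simply a miscalculation. The document does not support that, because 72% requires the whole 12-month loss to have occurred by week 2, and nothing in the text says so.

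The reply does not clear the passage, however. The figure 269 appears nowhere, and the only receiver count given is the one after loss. The margin is also thin: 80% is gone at about 3% loss by week 2 on the t-test, and no week-2 loss figure supports so small a loss.

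Two further points are fair.

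- The equal split across cells is an assumption. The strata are set for the women included, not for those who choose to receive a result.
- The sufficient-power sentence under methodological strengths is general. For 7 points, receivers versus decliners (215 v 105) has about 98% power, and high versus low PRS among receivers (about 107 v 108) about 95%. The sentence therefore needs qualifying for 2c only.

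Adjusting for baseline IES could also raise power. The article states no correlation between baseline and 2 weeks, so no figure can be put on that gain here.

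**Conclusion.** The point holds in a limited form. The 80% is not delivered by the loss-adjusted count printed beside it: 215 receivers give about 54 per group and about 72% power, or 80% power for about 7.7 points instead of 7. It is delivered by the implied count before loss, and so depends on an unstated assumption that almost no receiver is lost before the 2-week questionnaire. The defensible statement is a range for 2c of about 72% (full 20% loss by week 2) to 81% (no loss). That range rests on equal uptake and loss across the four cells and on the stated SD. The design, endpoint and recruitment target are unaffected.

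**What to change.** Restate the power sentence with the expected number per group at 2 weeks and the loss assumed by then. Suggested wording:

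*Assuming equal uptake and loss across the four PRS-by-disease groups, about 269 receivers are expected before loss (67 per group) and 215 at study completion (54 per group). For a 7-point IES difference at 2 weeks between affected and unaffected high-PRS receivers (SD 14.2, two-sided 5%), power is about 81% with no loss by 2 weeks and about 72% if the full 20% is lost by then. In the latter case the difference detectable with 80% power is about 7.7 points.*

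If the authors have an expected loss for week 2, they should state it and give the matching power. Under methodological strengths, qualify the sufficient-power sentence so that it carries this range for hypothesis 2c.

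The cost is wording only and a slightly less favourable stated figure. No extra recruitment is needed.

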#### Statistical analyses

For each of the main outcome variables (e.g. breast cancer anxiety), linear or logistic regression will be used as appropriate. Further multivariable analyses will be used to adjust for potential confounding variables (e.g. age, parity, stressful life events). Appropriate regressions will be performed to investigate whether outcomes differ between receivers and decliners (hypothesis 1a) and between subgroups of affected and unaffected women (hypothesis 2c) and those receiving either a low or high PRS (hypothesis 2b and 2c). Repeated measurements will be analyzed using linear mixed models to assess how outcomes change over time among receivers (hypothesis 2ai and 2b). This approach adjusts for the repeated measures per person and also allows for missing values.

## Discussion

To our knowledge this is the world’s first study to assess determinants for uptake of polygenic risk information, and the psychological and behavioral impact of receiving this information. Testing for polygenic risk will result in a paradigm shift in the practice of clinical genetics and oncology. Currently, genetic testing for hereditary cancer is offered in relation to personal and family cancer history, cancer type and/or other clinical criteria based on the likelihood of a pathogenic variant in high- penetrance gene being present, and these genes form the sole basis of the test. Because of this, the majority of women attending FCCs for hereditary breast cancer are not offered testing as they do not meet the minimum criteria for genetic testing. However, it is increasingly clear that breast cancer risk is also associated with other types of genetic risk (e.g. polygenic risk), often in the absence of additional family history for those women who are already affected by cancer. The inclusion of polygenic risk in FCCs will dramatically change service provision and allow access to personalized genetic testing to a wider group of women, including testing of women with breast cancer unselected for family history.

Findings from this study will also have implications for testing for common risk variants in other settings (e.g. hereditary cardiovascular disease and diabetes) and this study will provide a model for similar research across other important fields in medicine which are impacted by genomics.

### Methodological strengths and limitations

A substantive strength of this study is the large and diverse cohort available through the parent ViP study. The parent study aims to recruit every family in Victoria and Tasmania that attended a FCC to undergo genetic testing for hereditary breast cancer. The multicenter approach and diverse cohort will increase the external validity and generalization of the study findings. The sample size in the current study will provide sufficient power to detect clinically meaningful effects for the key outcome variable of breast cancer anxiety.

The study is a prospective study, which employs, wherever possible, validated measures that have been utilized previously with women at high risk for breast cancer. In applying this study design we hope to build a comprehensive picture of the psychological and behavioral outcomes associated with receiving polygenic breast cancer risk information.

Two potential limitations of the study must also be acknowledged. Firstly, it was beyond the capacity of the research to translate the patient questionnaires into other languages. Hence, women from non-English speaking backgrounds cannot be included. Secondly, this study will not involve development and assessment of pre-testing genetic counselling as the PRS results are available as part of the parent ViP study. The focus of this translational research is to explore the uptake of PRS results and psychological and behavioral outcomes associated with receiving or not receiving one’s PRS result. Future research will be able to explore pre-testing genetic counselling and the informed consent process including the provision of information of the benefits and limitations of SNP testing.

## Abbreviations

BRCA1/2: Breast cancer gene 1 and 2
FCC: Familial cancer clinic
PRS: Polygenic risk score
SNPs: Single nucleotide polymorphism
